## Abstract

**Background:**

Most randomized controlled trials of interventions designed to promote cancer screening, particularly those targeting poor and minority patients, enroll selected patients. Relatively little is known about the benefits of these interventions among unselected patients.

**Methods/Design:**

"Get Screened" is an American Cancer Society-sponsored randomized controlled trial designed to promote mammography and colorectal cancer screening in a primary care practice serving low-income patients. Eligible patients who are past due for mammography or colorectal cancer screening are entered into a tracking registry and randomly assigned to early or delayed intervention. This 6-month intervention is multimodal, involving patient prompts, clinician prompts, and outreach. At the time of the patient visit, eligible patients receive a low-literacy patient education tool. At the same time, clinicians receive a prompt to remind them to order the test and, when appropriate, a tool designed to simplify colorectal cancer screening decision-making. Patient outreach consists of personalized letters, automated telephone reminders, assistance with scheduling, and linkage of uninsured patients to the local National Breast and Cervical Cancer Early Detection program. Interventions are repeated for patients who fail to respond to early interventions. We will compare rates of screening between randomized groups, as well as planned secondary analyses of minority patients and uninsured patients. Data from the pilot phase show that this multimodal intervention triples rates of cancer screening (adjusted odds ratio 3.63; 95% CI 2.35 - 5.61).

**Discussion:**

This study protocol is designed to assess a multimodal approach to promotion of breast and colorectal cancer screening among underserved patients. We hypothesize that a multimodal approach will significantly improve cancer screening rates.

The trial was registered at Clinical Trials.gov NCT00818857

## Background

Poor, underserved-minority, and uninsured patients have lower rates of cancer screening than other Americans. Lower rates of screening contribute to disparities in cancer mortality. For example, African Americans have higher incidence of colorectal cancer (CRC), yet are screened at lower rates. This represents an example of the inverse care law (similar to the treatment-risk paradox[1]) whereby those with the greatest health care need (in this case higher need for screening) are least likely to receive care[2].

This unfortunate paradox in cancer screening likely results from a combination of fewer resources available to patients and fewer resources available to safety net practices serving poor, minority and/or uninsured patients. Underserved patients often face insurance[3,4] and other financial barriers,[5] in addition to barriers related to knowledge,[6,7] mistrust,[8] limited English proficiency (LEP),[9] self efficacy, [10-12] and health care literacy[13]. Underserved patients are more likely to be cared for in under-resourced practices[14-16].

There are two key challenges to development of interventions that improve cancer screening among underserved patients. The first challenge is conceptual and the second is methodological - sample selection bias. The conceptual challenge results from the finding that low-intensity cancer screening promotion interventions may not necessarily help close gaps in cancer screening, particularly if harder-to-reach groups respond at lower rates to these interventions. For example, a single reminder mailed out by health plans to patients who are soon due for cancer screening yields higher screening rates for patients with greater resources resulting in increased screening disparities[17].

One way to address the unintended consequence of increasing disparities is to invert the inverse care law and allocate greater resources to patients who face greater screening barriers. This approach has been successfully used to eliminate community-wide disparities in other preventive services, particularly immunizations[18]. In this case, Szilagyi et al implemented reminders, recall and outreach within safety net practices. They compiled practice-based registries, *among all eligible patients *(not a selected subsample) and implemented a combination of in-reach (clinician prompts at the time of patient visits) and outreach to patients past due using increasingly intensive interventions (letter, phone calls and even home visits) to families that failed to respond to less intensive interventions. We derived principles from their project and applied these principles to cancer screening.

### Principles for addressing disparities in cancer screening

We adapted the following four principles to promotion of mammography and colorectal cancer screening:

#### 1) Patients needing clinical services are identified using data from primary care practices

Although this approach does not reach all persons, i.e. those not registered at a primary care practice, it better targets resources to unscreened persons than broad-based community approaches. Also, most randomized controlled trials formally enroll patients, leading to sample selection bias because harder-to-reach patients are more difficult to reach for enrollment. Results from these trials - particularly those involving outreach - may not readily apply to harder-to-reach groups. By identifying patients from primary care practices and embedding the intervention in the care of randomly selected patient care, we skirt this potential bias.

#### 2) Resources are focused on practices that care for large numbers of underserved patients

Underserved patients often cluster within relatively few practices; focusing on these practices directs resources to where they are needed the most.

#### 3) Personal physician recommendations are leveraged to promote preventive services

Physicians almost universally endorse cancer screening[19]. However, high rates of physician recommendations for screening are not supported by either chart documentation [20] or patient report[21]. Clinicians' apparent failure to recommend cancer screening despite their best intentions is likely attributable to competing demands for their time and attention during busy offices visits,[22,23] such as management of multiple acute problems, chronic illnesses, psychosocial problems, completion of documentation, referrals, and phone calls. Competing demands reduce rates of the delivery of preventive services,[24,25] including cancer screening[26]. Prompting clinicians may help,[27,28] but is only relevant to patients who come in for care and clinicians may inadvertently disregard prompts[29]. Patient prompts combined with outreach to patients may complement clinician prompts at point-of-care.

#### 4) Outreach directs increasingly intensive interventions to those who have failed to respond to earlier interventions

This focuses more intensive resources on those who are harder-to-reach.

This project aims to address both conceptual and sample selection limitations. It adopts a multimodal approach to screening promotion and evaluates it through a randomized controlled trial with minimal selection bias in enrollment.

## Methods/Design

### Study design

We use a pragmatic, randomized controlled trial to evaluate this multimodal intervention with the patient as the unit of randomization. This allows for direct comparison of cancer screening rates (intervention vs. control groups) among patients who at the outset are past due for mammography or colorectal cancer screening. We chose to randomize at the patient level rather than physician or physician group level because it is difficult to ensure comparability when randomizing relatively small numbers of physicians or physician groups. It should be noted that patient-level randomization allows for physician learning effects, which bias results towards the null so results from this trial may be conservative.

The study design is shown in Figure 1. Individual patients are randomized and receive the 6 month intervention. Twelve months following randomization the delayed group also receives intervention. The primary analysis will be based on comparison of screening rates of patients in the early group who receive the intervention with those in the delayed group who receive usual care during the same time period. To account for lags between referral and completion of screening, rates of screening will be compared over 12 months.

**Figure 1 F1:**
[figure not shown]
**Patient flow**.

### Selection of practice site

We recruited one large safety net practice in Rochester, NY to participate in this trial. Given our aim of evaluating the impact of this multimodal intervention on disparities in cancer screening, we targeted a practice that serve large numbers of low-income and minority patients.

### Participant consent, eligibility and randomization

The study was approved by the Institutional Review Board of the University of Rochester. Participant informed consent was waived by the Institutional Review Board because the study poses no greater risk to participants than that associated with routine care, participants are free to ignore in-reach or outreach and may request that they receive no further reminders at any time.

Participant eligibility criteria for enrollment in the study include: (1) being a registered patient at the practice (we used a single download from the health system to create a practice registry); (2) having at least one visit to the practice in the past two years (to ensure participants were actively receiving care at the practice); (3) being ages 40-75 years for mammography screening, and 50-75 years for CRC screening; (4) being past due for annual mammography or CRC screening [(recommended intervals are 10 years for those screened through colonoscopy, 5 years for those screened with sigmoidoscopy and/or barium enema, and annually for those screened through fecal occult blood tests (FOBT)]. Women ages 50-75 could be enrolled based on either or both mammography and CRC criteria. Patients at higher risk for cancer due to prior cancer, premalignant conditions, inadequately evaluated breast mass, or positive FOBT were not randomized. Higher risk patients were excluded from randomization due to ethical concerns; clinicians were notified if chart review revealed they were overdue for screening.

Potentially eligible participants were identified using practice billing data based on age, sex and last visit to the practice. These data, in addition to race, ethnicity, presence and type of insurance, name of the primary care physician, and contact information were imported into a secure, customized patient tracking registry that was created in Microsoft Access^®^. Last dates of screening were determined through manual review of the electronic medical record (EMR) by research assistants using structured abstract forms to determine if, when and how participants were last screened.

After a research assistant determined eligibility, the off-site, statistician - blinded to all patient information not needed for stratification - assigned patients to early (intervention) or delayed (control) intervention using computer-generated random numbers. Randomization was stratified by screening type (mammography or CRC) to ensure that comparable groups of patients are randomized to each arm. Unique ID numbers were assigned to patients that identify their intervention group. The statistician maintained the key; all other study personnel were blinded to the intervention group assignment. The encoded sequences were affixed to the Case Report File (CRF) as well as the patient chart. Patients in both the intervention and control groups are followed for one year.

### Description of the intervention

The intervention, referred to as "Get Screened," builds on the finding that multimodal initiatives are more powerful for promoting use of preventive services[30]. We use paper prompts that are delivered to the clinician and patient immediately prior to the visit by office medical assistants. No more than three prompts are delivered for the same patient. One research assistant uses the EMR to indentify unscreened patients in the intervention group who have impending visits in during the week. She organizes patients by day of week into an accordion folder and delivers this to each suite within the large practice.

#### Clinician Prompt

We designed clinician-friendly, paper prompts that indicate that the patient is past due for mammography and/or CRC screening. We piloted the prompt sheet and obtained feedback from clinicians in the practice. CRC screening involves a number of different potential screening modalities[31]. Based on our discussions with community practices and local imaging centers, we have found that FOBT and colonoscopy were primarily used; flexible sigmoidoscopy, double contrast barium enema, and virtual colonoscopy were seldom used to screen for CRC locally. The back of each prompt sheet includes a brief summary of the relative advantages and limitations for each screening modality intended to facilitate clinician-patient discussion. The outreach worker also delivers fecal immunochemical testing kits to the practice and instructs medical assistants in how to counsel patients in their use and how to complete the test requisition. Fecal immunochemical tests and referral forms for colonoscopy are made available at the time of the patient visit.

#### Patient Prompts

We designed a simple patient prompt based on a low-literacy tool used to prompt patients to request pneumococcal vaccination[32]. We piloted the tool and received suggestions from our community-advisory board.

#### Patient Outreach

Outreach to unscreened patients consists of two personalized letters and up to four automated telephone reminder (ATR) calls. The letter is signed by the patient's primary care clinician and indicates that the patient is overdue for screening and why screening is important. It includes relevant phone numbers including how uninsured patients can obtain free screening. The automated telephone reminders are scripted, pre-recorded messages that include the patient's first name. The message identifies the caller and the practice; it then informs the patient s/he is past due and the phone number to call to schedule a screening (mammography) or an appointment (to discuss CRC). A completed call is defined as an answered call (either in person or a machine).

The first letter is sent within the first week of enrollment. This is followed by two completed ATRs at week 2 and 6 [33,34]. For patients who remain unscreened, a second letter is mailed out at week 12 followed by a third ATR at week 14. For patients past due for CRC screening, the letter includes a testing kit for fecal immunochemical testing for home use. A final ATR is made at week 26.

Both the letters and ATRs provide the phone number of the outreach worker if help is needed. Using a three way call option, the outreach worker can link patients with mammography schedulers or with the National Breast and Cervical Cancer Early Detection Program (NBCCEP), which provides free screening for the uninsured[35].

### Creation of patient tracking registry

We were unable to identify a commercially available tracking registry that met our study requirements. Hence, we designed our own registry using Microsoft Access^®^. The key functionalities of the registry include:

1) Electronic importation of data from billing data (patient name, age, gender, race, ethnicity, insurance type, primary care clinician, contact information, date of last patient visit).

2) Location on a secure university web server and restricted access to different fields based on unique passwords. For example, the outreach worker only has access to data for patients assigned to the intervention. Similarly, research assistants are blinded to group assignment and related data.

3) Tracking includes the date of all interventions (prompts, letters and phone calls) and date and type of cancer screening.

4) Report writing - ability to generate reports on patients based on types and dates of interventions received or other key fields.

5) Patient screening test results are used to update the registry facilitating removal of screened patients from further intervention.

### Description of usual care

All patients randomized to the delayed intervention receive "usual care" during the twelve months following randomization. In this practice, the clinician (family physician, nurse practitioner, or physician assistant) is responsible for discussing cancer screening with the patient and for initiating any referral or for handing out FOBT cards. The EMR has a section called health maintenance profile that allows for input of the last screening date to be entered and generation of alerts for future screening. However, discussion with clinicians suggests that this feature is not clinician-friendly and is seldom used due to time constraints. Instead, each clinician has his/her own method for tracking cancer screening. In our pilot site, many clinicians reported not having organized systems for contacting patients overdue for screening outside of scheduled visits.

### Baseline and follow-up measures

Table 1 lists the baseline measures abstracted by a research assistant who is blinded to group assignment. The primary outcome measure is medical record documentation of completed mammography or any type of CRC screening during the 12 months following randomization. Covariates including age, gender, race, ethnicity, insurance, number of visits in year prior to randomization and comorbidity (based on the number of problems listed on patient problem lists) will be used to compare key characteristics of early and delayed groups and test for interactions.

**Table 1 T1:** Baseline measures

*Category*	*Baseline Measure*
Demographics	Age (years), sex (male/female, race (White, African American/Black, Asian other), Hispanic ethnicity (yes/no), and insurance (yes/no) and if yes

Insurance	Any (Yes/No) Type (Private, Medicare, Medicaid), HMO (Yes/No)

Visit Utilization	Number of visits in year preceding randomization

Comorbidity	Number of conditions listed on patient problem list

Cancer risk	Breast cancer risk factors (prior breast cancer, BCRA, family history) CRC risk factors (Prior polyp, inflammatory bowel disease, genetic condition)

Cancer screening history	Date of last mammogram and results (Normal/Abnormal) Date, type, and results (Normal/Abnormal) of CRC screening: Colonoscopy FOBT Sigmoidoscopy Double contrast barium enema

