### Sample Size determination

For the main study, based on the size of the recruited practice and screening rates from the pilot study, we estimate that 190 patients will be past due for mammography and 239 will be past due for CRC screening. Based on our pilot data, we anticipate rates of screening of 18% and 10% respectively in the usual care (delayed group). Based on our pilot data, we conservatively estimate that this multimodal intervention will double screening rates for both mammography and CRC screening among those in the early intervention group. Based on these assumptions, we will have a minimum of 80% power to detect a difference of 18% in the mammography group and 13% in the colorectal screening group using 95% confidence intervals.

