### Patient accrual and study flow

Patient flow for the main study is shown in figure 1. Of the 525 women 40-75 years and men 50-75 years of age that had a visit during the past two years, 148 had undergone timely cancer screening. Of these and 10 were deemed higher risk and not eligible for randomization. A total of 367 patients will be randomized to the two groups.

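### As worded, the primary outcome counts tests that were not overdue and lets one test stand for two, and the power statement covers two test-specific comparisons instead of this outcome

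*Protocol article*

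**What the plan says.** All references are to the protocol article.

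- **Outcome** (Baseline and follow-up measures): "The primary outcome measure is medical record documentation of completed mammography or any type of CRC screening during the 12 months following randomization". This is a single measure, with no restriction to the overdue test and no rule for a patient overdue for both.
- **Entry** (Participant consent, eligibility and randomization): "Women ages 50-75 could be enrolled based on either or both mammography and CRC criteria". Mammography is treated there as annual.
- **Planning** (Sample Size determination): "we estimate that 190 patients will be past due for mammography and 239 will be past due for CRC screening". For usual care, "we anticipate rates of screening of 18% and 10% respectively in the usual care (delayed group"), and "we conservatively estimate that this multimodal intervention will double screening rates for both mammography and CRC screening". The power claim reads "minimum of 80% power to detect a difference of 18% in the mammography group and 13% in the colorectal screening group"; its error level is indicated only by the phrase "using 95% confidence intervals". No power is given for an either-test outcome.
- **Numbers** (Patient accrual and study flow): "A total of 367 patients will be randomized to the two groups".
- **Comparison** (Study design; Planned analytic approach): early and delayed groups are compared on screening rates, without saying whether that is one comparison or one per test.
- **Pilot** (Preliminary data): the odds ratio of 3.63 is for having any screening.

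**The concern.** The trial asks whether patients who are past due get screened. The outcome as written can be met without that happening.

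- **Tests not due.** A woman aged 50-75 who enters on the CRC criterion alone is current on an annual mammogram, so her next one falls due within the 12-month window. If she has it, she is a success although her CRC test is still undone. The reverse can also occur: a repeat annual stool test in a woman overdue only for mammography.
- **One test for two.** A woman overdue for both is a success after either test, so a gain in mammography alone can appear as a gain in screening overall.
- **Mismatch.** The planning rates of 18% and 10% are test-specific rates in two overlapping subsets. They are not rates of the stated outcome in the 367 randomised patients.

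The stakes are interpretability and some loss of sensitivity. If the choice between a combined and a test-specific result stays open until data are seen, selective reporting also becomes possible.

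**Working it through.** **Method.** Two proportions, two-sided 0.05 (inferred from the 95% intervals), 1:1 allocation (assumed; no ratio is stated). With d the difference, power = Φ[(d − 1.96·se₀)/se₁], where se₀ uses the pooled rate and se₁ the separate rates.

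**1. The plan's own figures.**
- Mammography, 95 per arm, 18% v 36%: 80.3% (81.4% with unpooled variance).
- CRC, 119.5 per arm, 10% v 23%: 77.6% (78.5% unpooled).

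Mammography reproduces, and CRC is within about 2 points. Both are test-specific comparisons.

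**2. Composition of the sample**, if the sample-size estimates and the accrual figure describe the same patients.
- Overdue for both: 190 + 239 − 367 = 62 (17% of 367).
- Mammography only: 190 − 62 = 128.
- CRC only: 239 − 62 = 177.

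**3. Either-test outcome with no not-due tests.** Rates double and the two tests are independent.
- Doubly overdue, control: 1 − 0.82×0.90 = 26.2%.
- Doubly overdue, intervention: 1 − 0.64×0.80 = 48.8%.
- All 367, control: (128×0.18 + 177×0.10 + 62×0.262)/367 = 56.98/367 = 15.5%.
- All 367, intervention: (128×0.36 + 177×0.20 + 62×0.488)/367 = 111.74/367 = 30.4%.
- Difference 14.9 points; power about 93%.

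**4. What success means for the 62.** Both tests are done in 0.18×0.10 = 1.8% of control and 0.36×0.20 = 7.2% of intervention patients. The share of successes with one overdue test still undone is (26.2 − 1.8)/26.2 = 93% in control and (48.8 − 7.2)/48.8 = 85% in intervention. With no CRC effect at all, either-test success would still rise from 26.2% to 1 − 0.64×0.90 = 42.4%.

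**5. Adding not-due mammograms.** Let w be the number of CRC-only women current on mammography and q the proportion who have the next mammogram, equal in both arms. Neither is given for the main trial.
- All men are CRC-only. With 70% women, as in the pilot, there are 0.30×367 = 110 men, so w = 177 − 110 = 67. With 60% women there are 147 men, so w = 30.
- The expected-success totals in step 3 rise by 0.90·w·q (control) and 0.80·w·q (intervention), so the difference falls by 0.10·w·q/367.

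| w | q | Control | Intervention | Difference (points) | Power |
|---|---|---|---|---|---|
| 0 | – | 15.5% | 30.4% | 14.9 | 93% |
| 30 | 30% | 17.7% | 32.4% | 14.7 | 90% |
| 67 | 50% | 23.7% | 37.7% | 14.0 | 83% |
| 67 | 70% | 27.0% | 40.7% | 13.6 | 79% |

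Not-due CRC tests in mammography-only women are left out because the documents give nothing to size them.

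**The case against.** **A test-specific reading is available.** The outcome sentence can be read as mammography for those overdue for mammography and CRC screening for those overdue for CRC. Stratification by screening type, the pilot's description of two arms and the separate power figures all point that way. On that reading, not-due tests and double counting drop out, and exact scoring may sit in a fuller document. This has weight, but the reading is nowhere stated, and the pilot's any-screening result points the other way. It would also leave two primary comparisons sharing about 62 patients with no stated alpha rule. Either reading needs the sentence reworded.

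**Stronger readings that the documents do not support.**
- *A collapse in CRC power.* A reader might apply the either-test outcome inside the 239 CRC patients, credit 67 women with 50% repeat mammography, and get 22.6% v 31.2%, with power falling from 58% (10% v 20%) to 32%. The article proposes no such analysis: an either-test outcome belongs in all 367, and a CRC-specific one excludes mammograms. The sum also omits the either-test rule for the 62 doubly overdue. With them included, the rates are 26.8% v 38.7%, so the difference rises to 11.9 points and power is about 50%.
- *An underpowered composite.* Under the planning assumptions and with no not-due tests, its power exceeds 90%.
- *Two incompatible primary outcomes.* Only one is stated. The any-screening result belongs to the non-randomised pilot, and giving power for components is a mismatch, not a contradiction.
- *A false effect.* Not-due tests that are equally frequent in both arms do not bias the randomised test.

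**Conclusion.** The point holds in moderate form. Followed literally, the outcome rewards tests that were not overdue and treats one test as enough for patients who needed two, and the stated power belongs to other comparisons. Over the range examined, the loss is 0.2 to 1.3 points of difference and about 3 to 14 points of power. The larger problem is interpretation: among the doubly overdue, most successes would leave one overdue test undone.

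The sizes rest on the 62-patient overlap, 1:1 allocation, independence of the two tests, and assumed ranges for the female share and for repeat mammography. The wording fault and the mismatch with the power statement rest on none of these. It should be corrected, but it does not invalidate the randomised comparison.

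**What to change.** 1. Reword the primary outcome so that only completion, within 12 months, of a test overdue at randomisation counts, and exclude not-due tests.
2. Score the mammography and CRC comparisons each on its own test among patients overdue for that test, with doubly overdue women entering both.
3. State whether the primary test is a single comparison of any overdue test completed in all 367 patients, or the two test-specific comparisons. Give the matching power and, if there are two, the alpha rule.

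**Cost.** Scoring needs no new data: baseline screening dates and types, and the date and type of later tests, are already recorded. The choice in step 3 does carry a price. Splitting alpha at 0.025 each lowers power to about 71% for mammography (18 points) and 68% for CRC (13 points). Two tests at 0.05 each without adjustment would allow a family-wise error of up to 1 − 0.95² = 9.75% if independent. A single overdue-test primary avoids both and has about 93% power under the planning assumptions, but it still counts a doubly overdue woman after one test. The test-specific results should therefore be reported beside it.

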### Planned analytic approach

Intervention vs. control groups will be compared based on intention-to-treat. That is, once randomized patients will be included in the analysis regardless of whether they leave the practice or not. We will use Generalized Estimating Equation models to control for covariates and clustering within practices. We also will assess whether expected baseline differences in screening by race, ethnicity and insurance are attenuated in the intervention group. We will use a difference in difference approach to assess whether the differences between Whites and Blacks, Hispanics and non-Hispanics, and insured and uninsured patients are significantly smaller in the intervention (early) compared to usual care (delayed group).

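### The named covariates include neither prior screening history nor the randomisation stratum, so the plan does not commit to using either in the adjusted analysis; the gain at stake is modest

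*Protocol article*

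**What the plan says.** Baseline and follow-up measures introduces the list with "Covariates including age, gender, race, ethnicity, insurance, number of visits in year prior to randomization and comorbidity" and says these "will be used to compare key characteristics of early and delayed groups and test for interactions". Table 1 in the same section also records cancer screening history: "Date of last mammogram and results (Normal/Abnormal", and the date, type and result of colorectal tests. That history does not appear in the covariate sentence.

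Participant consent, eligibility and randomization states "Randomization was stratified by screening type (mammography or CRC) to ensure that comparable groups of patients are randomized to each arm". The same section limits entry to patients "being past due for annual mammography or CRC screening" and adds: "Women ages 50-75 could be enrolled based on either or both mammography and CRC criteria".

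Planned analytic approach says "We will use Generalized Estimating Equation models to control for covariates and clustering within practices". It does not list the covariates or mention the randomisation stratum. Sample Size determination treats mammography (190 patients) and colorectal screening (239) as two groups with separate rates and detectable differences.

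**The concern.** Patients enter because they are overdue, but overdue covers both someone who has just missed a test and someone never tested. It is plausible that these patients differ in their chance of being screened in the next 12 months. The information is abstracted for everyone, because eligibility depends on it. If the primary model leaves it out, a chance imbalance between arms stays in the estimate and some precision is given up for nothing.

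The stratum raises a similar point. A factor that restricted the randomisation would normally be carried into the analysis. Here the only design feature the model names is practice, although Selection of practice site describes a single practice. The primary outcome is worded as mammography or any colorectal test, and the pilot was summarised as any screening, so a pooled analysis is a natural reading. In a pooled analysis, screening type is prognostic at the article's own rates. The two stated levels also overlap for women overdue for both tests, and the text does not say in which level they were placed.

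**Working it through.** **1. The plan's own power figures.** Inputs from Sample Size determination: 190 and 239 patients, control rates 18% and 10%, differences of 18 and 13 points. I assume 1:1 allocation (the ratio is not stated) and two-sided 5%. With n per arm and p̄ the mean of the two rates:

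power = Φ{[δ − 1.96·√(2p̄(1−p̄)/n)] / √([p0(1−p0)+p1(1−p1)]/n)}

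- Mammography, n = 95, 18% v 36%: (0.18 − 1.96×0.0644)/0.0631 = 0.852, power 80.3%.
- Colorectal, n = 119.5, 10% v 23%: (0.13 − 1.96×0.0480)/0.0473 = 0.759, power 77.6% (about 78.5% with unpooled variance).
- Colorectal, 10% v 20% (the assumed doubling): power 58.2%.

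The first matches the stated 80% and the second is close to it. None depends on covariate adjustment.

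**2. Gain from prior screening.** The article gives neither the share ever screened nor its association with later screening. Both are therefore assumed: 60% previously screened in the mammography group, 30% in the colorectal group, and an odds ratio (OR) of 2, 3 or 8 in each arm. Split each arm's rate p into rates for never screened and previously screened that satisfy the OR and average to p. With π the share previously screened and d the gap between the two rates in an arm, the proportional fall in variance of the risk difference is

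R = π(1−π)(d0² + d1²) / [p0(1−p0) + p1(1−p1)].

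Example, mammography at OR 3: 18% splits into 9.4% and 23.7%, and 36% into 21.8% and 45.5%. So R = 0.24×(0.1433² + 0.2373²)/(0.1476 + 0.2304) = 0.0184/0.378 = 4.9%. Extra patients to match = 190×0.0488/0.9512, about 10. Power with n = 95/0.9512 per arm is 82.2%.

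| Group | OR | R | Power before → after |
|---|---|---|---|
| Mammography, 18% v 36% | 2 | 2.1% | 80.3 → 81.1% |
| | 3 | 4.9% | 80.3 → 82.2% |
| | 8 | 13.5% | 80.3 → 85.7% |
| Colorectal, 10% v 20% | 2 | 1.6% | 58.2 → 58.9% |
| | 3 | 4.1% | 58.2 → 60.0% |
| | 8 | 14.2% | 58.2 → 64.9% |

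For colorectal at 10% v 23% and OR 8, R is 15.3% and power goes from 77.6% to 84.1%.

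These are large-sample values. In 400,000 simulated trials per setting (colorectal at 10% v 20%), a risk difference standardised over the two history levels had its variance cut by 1.5% and 1.0% at OR 2, 4.2% and 3.2% at OR 3, and 12.1% and 12.8% at OR 8 (mammography and colorectal respectively). The table is therefore slightly generous.

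**3. Gain from the stratum in a pooled analysis.** Weights 190/429 and 239/429 give a mean control rate of 13.5%. The share of outcome variance explained by screening type is [0.443×(0.18−0.135)² + 0.557×(0.10−0.135)²]/(0.135×0.865) = 1.3%. At 36% and 20% it is 3.2%. This counts women overdue for both twice, so it is only indicative.

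**4. Overlap.** Patient accrual and study flow randomises 525 − 148 − 10 = 367 patients. Sample Size determination expects 190 + 239 = 429 overdue tests. The difference, 429 − 367 = 62, is the approximate number of women in both levels.

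**The case against.** The strongest reply is that the covariate sentence is not the adjustment set. Its list is open, its stated use is baseline comparison and interaction tests, and a journal article may leave the full model to an analysis plan. That stands against any claim that the variables are excluded. What remains is that no other covariates are named anywhere, and the model section refers to covariates without saying which.

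A reader might infer that the analysis ignores the randomisation strata. The article does not support this. The sample size treats the two tests separately, and within a single-test analysis screening type is constant. The listed age and gender also settle the stratum for men (colorectal only) and for women aged 40-49 (mammography only). The gap concerns a pooled analysis and women aged 50-75.

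A reader might also infer that screening history is the strongest predictor. No section gives its association with later screening, and the overdue criterion narrows its range. Number of visits, already listed, could matter as much. At an assumed odds ratio of 1.5 the simulated gain is about 0.2% or less. If history is correlated with the listed covariates, its added gain is smaller than the table shows.

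Finally, leaving a prognostic variable out does not bias a randomised comparison, and leaving out a stratification factor tends to err on the conservative side. Both points stand: this is about efficiency, not validity.

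**Conclusion.** The point holds as a modest improvement. The text does not commit to using either the screening history it collects or the factor it stratified on. Exclusion is not proven.

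Using history would cut the variance of the risk difference by about 2% at an assumed odds ratio of 2, 4-5% at 3 and about 14% (13.5% to 15.3%) at 8. That is roughly 1 to 7 power points, and a little less in finite samples. These figures rest on assumed shares previously screened, assumed odds ratios and 1:1 allocation. In a pooled analysis the stratum alone explains about 1.3% to 3.2% of outcome variance at the article's own rates.

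The 58% colorectal power under doubling has a separate cause: doubling 10% gives a 10-point difference, not 13. Adjustment would raise it only to about 59-65%. Nor does this point call for a new allocation scheme, since the article describes randomisation as already carried out.

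**What to change.** Before outcomes are analysed, state the adjustment set of the primary model and include in it:

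- for the test analysed, prior screening, coded as never screened or time since the last test;
- in any pooled analysis of any screening, an overdue-status factor with three exclusive levels: mammography only, colorectal only, both.

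Report the effect as a covariate-standardised risk difference with its 95% confidence interval. In a logistic GEE, adjustment moves the target to a conditional odds ratio and helps through power rather than a smaller standard error. The standardised difference stays on the scale used for the sample size.

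Leave the allocation as it is, but document how women overdue for both tests were stratified. The variables come from data already abstracted, so the cost is analysis wording and one sentence on the strata.
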